# Evaluation of FindMyApps: protocol for a randomized controlled trial of the effectiveness and cost-effectiveness of a tablet-based intervention to improve self-management and social participation of community-dwelling people with mild dementia, compared to usual tablet use

**DOI:** 10.1186/s12877-021-02038-8

**Published:** 2021-02-24

**Keywords:** Dementia, Social health, Psycho-social care, Quality of life, Digital health technology

## Abstract

**Background:**

For the rising number of people living with dementia, cost-effective community-based interventions to support psychosocial care are needed. The FindMyApps intervention has been developed with and for people with dementia and their caregivers, to help them use tablets to facilitate self-management and engagement in meaningful social activities. A feasibility study and exploratory pilot trial evaluating FindMyApps have been carried out. This definitive trial further evaluates the effectiveness of the intervention and, for the first time, the cost-effectiveness.

**Methods:**

A randomized controlled non-blinded single-center two-arm superiority trial will be conducted. Community-dwelling people with Mild Cognitive Impairment (MCI), or dementia with a Mini Mental-State Examination (MMSE) of > 17 and < 26, or Global Deterioration Scale 3 or 4, with an informal caregiver and access to a wireless internet connection will be included. In total, 150 patient-caregiver dyads will be randomly allocated to receive either usual care (control arm – tablet computer; *n* = 75 dyads) or usual care and the FindMyApps intervention (experimental arm – tablet computer and FindMyApps; n = 75 dyads). The primary outcomes are: for people with dementia, self-management and social participation; for caregivers, sense of competence. In addition to a main effect analysis, a cost-effectiveness analysis will be performed. In line with MRC guidance for evaluation of complex interventions a process evaluation will also be undertaken.

**Discussion:**

Results of the trial are expected to be available in 2023 and will be submitted for publication in international peer-reviewed scientific journals, in addition to conference presentations and reporting via the EU Marie Sklodowska-Curie DISTINCT ITN network. By providing evidence for or against the effectiveness and cost-effectiveness of the FindMyApps intervention, the results of the trial will influence national implementation of FindMyApps. We hope that the results of the trial will further stimulate research and development at the intersection of technology and psycho-social care in dementia. We hope to further demonstrate that the randomized controlled trial is a valuable and feasible means of evaluating new digital technologies, to stimulate further high-quality research in this growing field.

**Trial registration number:**

Netherlands Trial Register: NL8157; registered 15th November 2019.

## Background and rationale

In the Netherlands, 280,000 people live with dementia. This number is anticipated to more than double to 620,000 in 2050 [1]. Almost three quarters live at home. Whilst many people with dementia live well and independently for many years following diagnosis, many become increasingly dependent on support from relatives as the disease progresses. Of those people living with dementia, 70% stop their daily activities due to lack of confidence, 50% avoid community interaction due to concerns about their functional limitations and 40% hardly leave their home [2, 3]. More than half of all caregivers feel heavily or very heavily burdened by caring for someone with dementia [4].

Dementia greatly impacts people’s quality of life and their social health. Social health consists of three domains: capacity to fulfill one’s potential and meet obligations; ability to manage one’s own life to engage in meaningful activities; and ability to participate in social groups [5, 6]. Health and quality of life outcomes for people with dementia depend on many factors [6–10]: personal factors such as personality, competencies and skills; disease factors, such as specific disabilities and comorbidities; social factors such as competence of caregivers, care needs or living situation; and environmental factors such as living in a non-stigmatizing, dementia-friendly community, or the availability of assistive technologies [11, 12]. Strategies to optimize the influence of these factors are almost certain to improve the social health and quality of life of people living with dementia and their caregivers, which can support people living for longer in their own home [6, 13].

eHealth interventions may be able to play a role in improving social health in dementia. The World Health Organization report, *Dementia: a public health priority*, cites examples of the use of eHealth interventions [10]. The Dutch Dementia Care Standard also specifically identifies the appropriate implementation of eHealth interventions as having the potential to support people with dementia to live in their own homes longer and in better health [14]. Millions of applications (apps) for hand-held touch screen devices (including smartphones and tablets) exist, that have been designed to help people engage in pleasurable and meaningful activities, manage everyday life and maintain their social networks. There is growing evidence that apps also have potential in supporting people with mild dementia for the same purposes [15–18]. Examples of relevant apps available in the Netherlands include Ongehinderd (which allows users to search for accessible and disability-friendly locations and activities in the Netherlands), FaceTime (which for users of Apple devices allows them to conduct video calls), and a range of brain-training apps and games [19, 20]. Such apps may have the most impact in the early stages of dementia, although with respect to computerized cognitive training, it should be noted that there is no high-quality evidence from randomized controlled trials for benefits to activities of daily living or quality of life in MCI or dementia [21, 22]. Professional care is often not offered or accepted in the early phases of dementia, yet people will already be facing significant challenges in managing daily life [23].

However, it has also been noted that there are significant challenges to the implementation of eHealth interventions in general, and tablet-based interventions specifically, for people with dementia. Many people living with dementia are unfamiliar with the use of tablets or with how to download and use tablet-based apps, and only certain apps are sufficiently user-friendly for people with dementia [24, 25]. A necessary prerequisite to realizing the potential value of usable and suitable apps would be to support people in finding apps that meet their individual needs and preferences [15].

The FindMyApps intervention was designed specifically to meet that need, in co-creation between end users (people with dementia and their caregivers), Saxion University of Applied Sciences, Eumedianet, VUmc and Radboud UMC. The development process for FindMyApps has been fully described elsewhere in the literature [26–28]. The process began with identifying the needs of those with dementia and their caregivers, following which a user-centered design process resulted in a prototype that then underwent feasibility testing and was subject to a pilot randomized controlled trial. The intervention comprises three components: training in the use of a tablet and tablet-based apps, which is based on the ‘Errorless Learning’ method, the FindMyApps app and a cloud-hosted database of user-friendly apps. The FindMyApps app functions as a personalized selection tool: people with dementia (and their caregivers) can use the app to search the database for apps for self-management and meaningful activities that fit their needs, abilities and interests. The feasibility of the FindMyApps intervention has been tested on a small scale but the effectiveness in promoting self-management and social participation, as essential components of good social health, compared to the impact of a standard tablet has not yet been investigated. Through this randomized controlled trial, we will evaluate the effectiveness of FindMyApps. In line with the Medical Research Council framework for the evaluation of complex interventions, we will also carry out a process evaluation, to understand factors that facilitate or impede the implementation of FindMyApps [29]. Finally, we will carry out a cost-effectiveness analysis and compare the cost-effectiveness of FindMyApps to published analyses of other interventions designed to improve self-management and social participation.

This publication is based on version 2.1 of the study protocol, agreed as of 14-05-2020.

## Objectives

This RCT follows feasibility and exploratory pilot studies into FindMyApps, as a next phase in the Medical Research Council’s (MRC) framework for the evaluation of complex interventions.

The objectives of this study are:
To evaluate the effectiveness of FindMyApps, compared to usual care (tablet use without FindMyApps), in an RCT with respect to the following outcomes:
Persons with dementia: (primary outcomes) ability to self-manage and social participation, (secondary outcomes) experienced autonomy, neuropsychiatric symptoms and quality of life (health related);Caregivers: (primary outcome) sense of competence, (secondary outcomes) attitudes to dementia, experience of providing care and quality of life (health related).To evaluate the cost-effectiveness of FindMyApps compared to usual care/tablet use without FindMyApps.To conduct a process evaluation of the implementation of the FindMyApps intervention in the context of this study, in line with the MRC Framework for process evaluation [30], to identify factors relating to context, implementation and mechanisms of impact (usability, learnability and adoption) that may influence the outcomes of this study.

## Trial design

This is a randomized, controlled, non-blinded superiority trial with two parallel groups and two measurements (before the start of the intervention and after three months).

Alongside the effectiveness evaluation, a cost-effectiveness analysis and a process evaluation will be carried out.

The trial is registered in the Netherlands Trial Register: NL8157.

### Study setting

The FindMyApps intervention has been developed in the Netherlands with Dutch language and cultural content. This study focuses on the implementation of FindMyApps with community dwelling people in the Netherlands with MCI, confirmed at a memory clinic, or mild dementia, and their informal caregivers. Participants will be recruited nationally through a range of health and welfare organizations. The study investigators implementing the interventions and collecting data are based at Amsterdam UMC, location VUmc.

### Eligibility criteria

Study participants must provide written, informed consent before data collection for the study takes place (see Appendix 1 for sample Informed Consent Form). Participants are assumed to have capacity to consent, unless the researcher informing the participant and documenting their consent believes that there is evidence that the person is unable to understand the information provided about the study, or to retain the information for sufficient time to weigh the information and communicate their decision.

Eligibility of dyads recruited to the study is assessed primarily based on the person with dementia or MCI. However, caregivers must also be willing and able to fully participate and support the person with dementia in the study.

People with MCI or dementia must meet the following inclusion criteria at randomization: Age ≥ 18 year; either a current diagnosis of MCI (confirmed by memory clinic), or a current diagnosis of mild dementia of any etiology; community-dwelling; has access to a wireless internet connection in their home; has a caregiver (for example a spouse, child, other relative, neighbor, etc.) who also provides consent to participate in the study, does not have a diagnosis of dementia or MCI and either co-habits with the primary participant or spends at least one hour with the primary participant, on at least two separate occasions per week, every week. We recommend that the caregiver and primary participant practice together with the tablet twice a week. The caregiver must be available to support the person with dementia or MCI if they need help. That is why a caregiver must have contact with the participant at least twice per week. If the potential participant’s diagnosis is dementia (rather than MCI) then they must have either an MMSE < 26 and > 17, measured within the last three months, or a general deterioration scale (GDS) of 3 or 4, measured within the last three months. When used for diagnostic screening, an MMSE cut-off of 24 has been associated with high sensitivity and specificity for detecting dementia [31]. In this research the MMSE is not used for diagnostic screening, but to provide an up-to-date baseline with respect to cognitive function. All participants have a pre-existing diagnosis. For the purposes of this study, we have adopted a cut-off of 25 to provide additional sensitivity, at the expense of some specificity, whilst still avoiding a ceiling effect. The MMSE is widely used to assess cognitive decline but the GDS is also a reliable method to measure cognitive decline, with an internal-consistency reliability, α = 0.88 [32].

Exclusion criteria at point of screening: current diagnosis of Primary Progressive Aphasia (PPA); blindness or sufficiently severe visual impairment to make viewing content on a tablet screen impossible; insufficient competence in reading or listening modalities of the Dutch language to understand the information provided in the informed consent process; currently participating in another interventional research study or clinical trial with the potential to confound the results of both studies.

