### Sample size

Two pilot randomized controlled trials preceded this definitive trial, both of comparable design with comparable outcome measures [36, 37]. Values of partial eta squared with respect to primary outcomes measured with instruments which will also be used in the present study, were found to range from 0.01 (MSPP) to 0.38 (PAL). These correspond to small to large effect sizes, respectively, when compared to Cohen’s suggested benchmarks [38]. Previous evaluations of interventions implemented in the Netherlands to improve social health in dementia have also found moderate to large effect sizes, with respect to similar outcome measures [39, 40]. Whilst both pilot studies also revealed small between group differences with respect to a number of outcomes, this trial will not be powered to detect small effects of the intervention. We do not believe that small effects of the intervention – even if statistically significant – would be ‘clinically’ significant. We therefore do not feel that we could justify the additional use of public funds to conduct the trial in such a way as to have adequate power to detect small effects of the intervention.

Effects of the intervention on primary outcomes for the primary participants (social participation and self-management) will be tested using MANCOVA. An a priori power calculation was conducted using the software G*Power, version 3.1, for main effects MANOVA, assuming two dependent variables, two groups, alpha = 0.05 and power = 0.8, and a moderate overall effect. The total required sample size would be *n* = 158. This is an overestimate of the required sample size to achieve a power of 0.8 because the inclusion of covariates in the MANCOVA is expected to increase the statistical power of the test compared to MANOVA (thereby reducing the required sample size for the desired power of 0.8).

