### Recruitment

Recruitment will take place nationally throughout the Netherlands.

Participants will be recruited: via national networks of Meeting Centers, Alzheimer Cafes, memory clinics and day centers; through the Alzheimer Centre and Centre for Elderly Care Medicine of the Vrije Universiteit Medical Centre (VUmc) in Amsterdam; and through the website and social media platforms of the study, Alzheimer Nederland and other stakeholders.

The center for geriatric medicine (COGA) and Alzheimer Center of Amsterdam UMC, location VUmc, will support recruitment from their patient populations, by providing access to existing databases of eligible patients with an interest in research and by informing newly diagnosed patients who may be eligible for the study.

Interested participants will also be able to self-refer for eligibility screening via online channels, including the project website, the website of Dutch national dementia association Alzheimer Nederland and the websites of various smaller interest groups, organizations and charities.

National recruitment will continue until the required sample size has been met. It is expected that the recruitment period will extend over 23 months (100 weeks). In a previous pilot study, which was mainly conducted in two regions in the West and East of the Netherlands, 59 dyads were recruited over 12 months. Eighteen dyads were recruited in the final 12 weeks of the inclusion period for the pilot study, once relationships with referrers and public awareness were better established. The present national study can build on the network of referrers that was developed in this pilot study. Assuming at least the same average rate of inclusions for the duration of this study, and taking into account the larger recruitment area, this should allow for sufficient inclusions in the intended period.

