### Allocation

Participants will be randomly assigned to either the FindMyApps (experimental) or usual care (control) arm. Randomization will be performed via Castor EDC, following a variable blocked randomization method, with a target of 1:1 allocation and randomly selected block sizes of 4 or 6. Group allocation will be stratified on the basis of diagnosis (MCI or dementia) and any prior experience with the use of a tablet (participant self-report; ‘Yes’ or ‘No’).

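### Dyads who received FindMyApps in an earlier pilot remain eligible for either arm, and the prior-tablet-use stratum does not identify them (minor)

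*Protocol article*

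**What the plan says.** The article's Eligibility criteria section gives four exclusions. Three concern aphasia, vision and command of Dutch. The fourth bars a person "currently participating in another interventional research study or clinical trial with the potential to confound the results of both studies". Nothing in the inclusion or exclusion criteria, for the person with MCI or dementia or for the caregiver, refers to earlier FindMyApps participation or use.

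The article also establishes that earlier users exist. Objectives: "This RCT follows feasibility and exploratory pilot studies into FindMyApps". Sample size: "Two pilot randomized controlled trials preceded this definitive trial". Recruitment reports that in one previous pilot "59 dyads were recruited over 12 months".

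Some recruitment routes could reach these people again. "The present national study can build on the network of referrers that was developed in this pilot study". Two centres help "by providing access to existing databases of eligible patients with an interest in research". And "Interested participants will also be able to self-refer for eligibility screening via online channels".

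The nearest stratification factor (Allocation) is "any prior experience with the use of a tablet", recorded as yes or no. The Blinding section commits the researchers to limiting how much control participants learn about FindMyApps.

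**The concern.** The trial compares FindMyApps with tablet use without FindMyApps. A control dyad trained on FindMyApps in a pilot has already had the experimental intervention. An experimental dyad with the same history may start from a baseline that already holds part of the effect. Either way the dyad may add less than a full contrast, which pulls the estimate toward no effect.

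Such a control dyad also already knows what the other arm receives. That works against the masking effort, in a trial whose outcomes are unblinded self-report.

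The authors did consider confounding from other research, but limited the rule to concurrent studies. An earlier FindMyApps trial, the study most directly able to affect this comparison, falls outside it.

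**Working it through.** **1. Is a former pilot dyad eligible?**
- The research exclusion applies to current participation only, so a finished pilot does not trigger it.
- A person with dementia must have an MMSE above 17 and below 26, or a GDS of 3 or 4, measured within three months. This removes some former participants. It does not apply to people with MCI.
- Allocation stratifies on any tablet use. A dyad trained on FindMyApps and a dyad with ordinary tablet experience both answer yes.
- Baseline scores are covariates in the MANCOVA (Data management and analysis). They adjust for starting level. They do not restore a contrast that earlier exposure has removed.

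The gap in the text is therefore real.

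**2. The plan's own figure.** Inputs from Sample size: two outcomes, two groups, alpha 0.05, power 0.80, moderate effect. Moderate is taken as f² = 0.0625 (assumption). For the two-group MANOVA:

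power = P[F(2, N − 3; λ) > F₀.₉₅(2, N − 3)], with λ = N × f²

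At N = 158, λ = 158 × 0.0625 = 9.875 and power is 0.802. At N = 157 it is 0.799. The smallest N reaching 0.80 is 158, as stated in the article.

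**3. Dilution at the planned 150 dyads, before dropout.** Let m be the number of exposed dyads, split equally over the arms, and c the share of the contrast that each loses. The effect shrinks by s = 1 − c × m/150, so f² becomes 0.0625 × s². Both m and c are assumptions; the documents give neither.

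| m | c | s | f² | λ = 150 × f² | Power |
|---|---|---|---|---|---|
| 0 | – | 1.00 | 0.0625 | 9.375 | 0.780 |
| 6 | 1 (no contrast left) | 0.96 | 0.0576 | 8.640 | 0.743 |
| 15 | 1 | 0.90 | 0.0506 | 7.594 | 0.684 |
| 6 | 0.5 (half left) | 0.98 | 0.0600 | 9.004 | 0.762 |
| 15 | 0.5 | 0.95 | 0.0564 | 8.461 | 0.734 |

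**4. How plausible is m = 15?** The 59 dyads are taken to be all dyads of a randomised pilot, not only those given FindMyApps. With 1:1 allocation (assumption) about 30 were allocated to it. The article gives pilot dropout rates of 12% and 37% without saying which belongs to this pilot. Completers would then be between 30 × 0.63 ≈ 19 and 30 × 0.88 ≈ 26. Fifteen re-entrants from this pilot would be 15/26 ≈ 58% to 15/19 ≈ 79% of them, so 15 is a high figure for this pilot alone. The size of the other pilot is not given.

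**The case against.** Nothing in the article says that former pilot dyads will be approached or will enrol. The network of referrers consists of organisations, not past participants. The recruiting centres will also inform newly diagnosed patients. The 59-dyad pilot ran mainly in two regions, whereas this trial recruits nationally. The article rests on protocol version 2.1, which is not shown and might contain a screening check. All of this stands, and it limits how likely the problem is. It does not close the gap, because the article prints its eligibility list in detail and the list as printed admits these dyads.

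Zero contrast is a worst case. The intervention and trial procedure were improved after the pilots, and re-entrants in the experimental arm would get new training. Nothing shows that the effect of earlier exposure persists in this population. This too stands, which is why the half-contrast rows are given. The article also says that covariates should raise power above the MANOVA figure, so the absolute power values may be low.

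A reader might infer that pilot dyads will in fact carry exposure into both arms, or that up to 59 could do so. The documents support neither: enrolment is only possible, and only dyads allocated to FindMyApps are known to be exposed. Later access for pilot controls is not described. A reader might also infer a biased allocation. Randomisation balances exposed dyads between the arms in expectation, so systematic imbalance does not follow.

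The Blinding section promises efforts to limit awareness, not its absence. A few aware controls weaken that effort but do not contradict the text.

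**Conclusion.** The concern holds as a gap in the eligibility criteria: a dyad that received FindMyApps in a pilot can be randomised to either arm without being identified. The consequences are possible dilution toward no effect and weaker masking of controls.

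The size is unknown and may be nil. In the illustration, the loss of power at 150 dyads runs from none, through about 2 to 4 percentage points with 6 exposed dyads, to about 5 to 10 points with 15. This rests on f² = 0.0625, an equal split over the arms, no dropout, and a lost contrast of one half to all. Nothing stated in the article is numerically wrong on this point, and its sample size of 158 reproduces. Priority: minor.

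**What to change.** Add an exclusion to the Eligibility criteria for dyads in which either member has previously used FindMyApps or was allocated to it in an earlier study. Check it with one screening question and, where available, the pilot participant lists.

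If such a dyad has already been randomised, keep it in the intention-to-treat analysis and add a sensitivity analysis that leaves it out.

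The cost is one line of text, one question, and the loss of a few willing dyads to recruitment.
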